### Facebook App

In this part we will describe the implementation of the survey and data collection using the custom made Facebook app. The Facebook app has several advantages over more traditional online surveys. First, it offers the possibility to customize the procedure and randomize some of its steps, which will be a useful feature for this study. Second, it allows automatic calculation of participants’ scores and instant customized feedback for each participant, which acts as a motivator for participation. Third, it allows us to collect some of the Facebook data that will be crucial for our exploratory part of the study (i.e., predicting the moral foundations). Finally, it facilitates the dissemination of the study by allowing the participants to share their scores and invite others to participate. A clickable URL will take participants to a custom-made Facebook app that will host the survey. The survey will include measurements of moral foundations, moral identity internalization, attitudes toward CB, descriptive social norms and CB in addition to relevant (in)congruent calls-to-action for the charities. The charities will be used based on the pre-study results. The wireframe of an app is presented in Figure A1 in Appendix A.

However, as noted in the introduction, it is perfectly possible to conduct the study based on this research protocol without collecting Facebook data or developing the custom Facebook app. In this case one could simply use one of the many existing research platforms to create the survey and disseminate it over different online platforms.

### Pre-study

For the pre-study purposes, all the measures except the MFQ were translated into German, Dutch, and Italian (i.e., the calls-to-action, Moral Identity Internalization Scale and the measures of attitudes and social norms) The translated copies of the MFQ were already publicly available on the original authors’ website^4^. The translation of the other scales was done using a forward and back translation method, in which a native speaker first translated the original version of the measure from English to the target language (German/Dutch/Italian), trying to keep conceptual rather than literal meaning. Next, a separate bilingual speaker translated the translation back to English. Finally, the group of authors reviewed and compared the translations. Consensus among the authors was reached before continuing with pilot testing.

After translation of the materials, we conducted the pre-study (*N* = 50). There were several goals of this pre-study. First, we confirmed that there were no ambiguities and confusions regarding the translations and instructions. Second, the pilot study was used to check the appropriateness of the calls-to-action which are the main independent variable. Specifically, we wanted to receive feedback on whether our calls-to-action were perceived as being based on the individualizing and binding moral foundations. To do this, we first briefly familiarized our participants with the MFT and each of the moral foundations. Thereafter, we asked them to estimate on a seven-point scale the degree to which each of the calls-to-action rely on each of the five foundations. As we specifically created our calls-to-action using words from the *Moral Foundations Dictionary* (it can be found online: http://moralfoundations.org/othermaterials), we expected that our individualizing calls will be estimated to rely mostly on the Care/Harm and Fairness/Cheating foundations. Accordingly, we expected binding calls to be estimated to rely more heavily on the Loyalty/Betrayal, Authority/Subversion, and Sanctity/Degradation foundations.

Third, we wanted to examine whether different charities were perceived as being more acceptable for liberals, more acceptable for conservatives or universally acceptable. Specifically, we listed brief descriptions of 12 different charities and asked participants to estimate whether they thought they would be more acceptable for liberals or conservatives, scored on a 7-point-scale (−3 = liberal, 3 = conservative). The final goal of the pre-study was to test the main dependent variables of donating time and money. Specifically, we wanted to estimate the proportion of participants that were willing to donate any portion of money and time. Participants were asked to imagine that they had won a £/€50 Amazon gift card. Consecutively, they were asked whether they were willing to donate money out of this £/€50 to one of the charities that had previously been described and if they were interested in volunteering for one of these charities.

Generally, results of this pre-study indicated that the estimations of our calls-to-action were in the intended directions. Specifically, the individualizing call-to-action was estimated to be substantially more in line with the Care/Harm (*M* = 5.58; *SD* = 1.50)and Fairness/Cheating (*M* = 4.88; *SD* = 1.52) foundations than was the binding call-to-action (Care/Harm: *M* = 3.92; *SD* = 2.11; Fairness/Cheating; *M* = 3.82; *SD* = 1.60). Conversely, the binding call-to-action was estimated to be substantially more in line with the Loyalty/Betrayal (*M* = 4.50; *SD* = 1.64), Authority/Subversion (*M* = 4.90; *SD* = 1.82), and Sanctity/Degradation (*M* = 3.38; *SD* = 2.02) foundations than the individualizing one (Loyalty/Betrayal: *M* = 3.32; *SD* = 1.71; Authority/Subversion: *M* = 2.72; *SD* = 1.75; Sanctity/Degradation: *M* = 2.74; *SD* = 1.70). Estimations for the neutral call-to-action were between these two estimations for each foundation (Figure C1 in Appendix C).

Furthermore, results indicated that participants mostly perceived the charities as being more appropriate for liberals than conservatives, with several charities perceived as being more or less ideologically neutral (see Figure C2 in the Appendix C). For example, *European association for cancer research, Eurochild* and *MAGmine* were perceived to be relatively neutral, while the *Group for transcultural relation* was perceived as the most liberal one. These results can be used by any researcher that decides to draw on this protocol for studying CB. Finally, 86% of the participants in the pre-study were willing to donate at least some money out of this £/€50 (*M* = 19.84; *SD* = 15.67), and 78% were interested in volunteering for one of the charities (*M* = 4.00; *SD* = 2.21).

### The Independent Variables

#### Moral Foundations

Participants’ moral foundations will be assessed using the latest version of the MFQ (Graham et al., 2008; see http://www.moralfoundations.org for more information and to access the questionnaire). The questionnaire comprises 30 items, asking participants about the extent to which different factors are relevant in their moral decision-making. Each of the five foundations is assessed with six items, and the participants’ task is to evaluate the relevance of an item or agreement with the item on a six-point scale (0 = not at all relevant/strongly disagree; to 5 = extremely relevant/strongly agree). To obtain the final score on each of the subscales, the evaluations are summed up and consecutively divided by the number of items related to the particular subscale. A score between 0 and 5 will be calculated for each of the moral foundations subscales. The internal consistencies of the subscales were reported to be α = 0.69 (Harm), α = 0.65 (Fairness), α = 0.71 (Ingroup), α = 0.74 (Authority) and α = 0.84 (Purity) (Graham et al., 2011). The MFQ is open-access and freely accessible for research purposes.

#### Moral Identity Internalization

Moral identity internalization will be measured using a five-item subscale (“Internalization” subscale) of Aquino and Reed (2002) “Moral Identity Scale”. This scale is also open access for researchers. The Internalization scale measures the degree to which moral traits are central to an individual’s self-concept. The participants’ task is to evaluate every item using a 5-point Likert scale (1 = strongly disagree; to 5 = strongly agree). The internalization scale has been shown to have good internal consistency with α = 0.73.

#### (In)congruent Calls-to-Action

We designed three types of calls-to-action with the goal of having one that is neutral, one that is congruent with liberals’ moral foundations and one that is congruent with conservatives’ moral foundations. The assumption is that most participants will be grouped into two categories: those who mostly rely on individualizing foundations, and those who mostly rely on binding foundations. Thus, two types of morally relevant calls-to-action were used. The first emphasized individualizing foundations of Care/Harm and Fairness/Cheating, whereas the second one emphasized binding foundations of Loyalty/Betrayal, Authority/Subversion and Sanctity/Degradation. The final, neutral, call-to-action was constructed without involving any moral foundations. The proposed morally (in)congruent and neutral calls-to-action are presented in Table 1. We are presenting hypothetical calls to donate to two of the charities we used in the pre-study, *Eurochild* and *City of Sanctuary*. Incidentally, one is also estimated to be more liberal (i.e., *City of Sanctuary*), while the other appears to be relatively ideologically neutral (i.e., *Eurochild;* Figure C2 in Appendix C).

**Table 1 T1:** Calls-to-action that are going to be used in the study.

Individualizing call-to-action	**Show us your compassion** by supporting *City of Sanctuary/Eurochild* in achieving their goal *to care for refugees/protect children’s well-being*. Helping **vulnerable** *refugees/children* and **preventing suffering** is the **right thing to do**. By supporting *City of Sanctuary/Eurochild* you will get the chance to **increase fairness** and **justice and reduce harm** all over the world. Show us that you **care for others** and **make a difference** now! ^∗^In similar studies, the majority of people decided to donate some of the money should they win it. (included only in the social-norm condition).
Binding call-to-action	**Show us your integrity** by supporting *City of Sanctuary/Eurochild* in achieving their goal to *support refugees/promote children’s well-being.* **Protecting** innocent refugees/children and their families is your **civil duty**. By supporting *City of Sanctuary/Eurochild* you will get the chance to **follow proud religious and national leaders doing their obligation.** Show us that you are a **responsible community member** and **join the fight** now! ^∗^ In similar studies, the majority of people decided to donate some of the money should they win it. (included only in the social-norm condition).
Neutral call-to-action	Support *City of Sanctuary/Eurochild* in achieving their goal to *support refugees/promote children’s wellbeing*. You can help make a real difference to this very important issue. By supporting *City of Sanctuary/Eurochild* you will play an active role in finding a peaceful outcome. Show us that you are willing to support the cause now! ^∗^ In similar studies, the majority of people decided to donate some of the money should they win it. (included only in the social-norm condition).

*Bolded words represent the individualizing and binding moral frames. Italicized words pertain to the charity dealing with refugees and children, respectively.*

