#### Changing Behavior by Changing Social Norms

In addition to changing attitudes toward CB, a fruitful approach may be to influence perceptions of social norms about CB. Social norms are the perceived rules of a community or group that dictate desired behavior (Kandori, 1992). Although some studies show that norms are the weakest of the TPB predictors (see Armitage and Conner, 2001), others have pointed out the need to distinguish between several types of norms before assessing their contribution to behaviors. Specifically, three distinct types of normative influences have been identified. First, norms can be *injunctive*, representing the information about what most others approve or disapprove. Second, norms can be *descriptive*, conveying information about what most others actually do (Cialdini et al., 1990). Finally, personal injunctive norms, or moral norms can be defined as *individual internalized moral rules* (Smith and McSweeney, 2007; van der Linden, 2011). Thus far, several studies have investigated the role of different types of norms on prosocial behavior, showing mixed results (e.g., Shang and Croson, 2009; van der Linden, 2011).

Several studies showed that moral and injunctive norms significantly predicted charitable intentions, after controlling for attitudes, perceived behavioral control and past behavior (Smith and McSweeney, 2007; van der Linden, 2011). However, in these studies, descriptive norms did not have a significant influence on charitable giving. In contrast, other studies have shown that descriptive norms can be significant determinants of CB and prosocial behavior in general. For example, Shang and Croson (2009) demonstrated that providing individuals with information about the amount of money that others donated, influenced the amounts donated in public radio fundraising, both immediately and in renewals the year after. Moreover, Croson et al. (2009) showed that the effect of providing social information in such a way on donations to public radio is fully mediated by changes in the perception of descriptive social norms. It is possible that these mixed findings are the result of differences in the saliency of norms that were used in those studies.

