#### Normative Information

Normative information will either be included or omitted in addition to the calls-to-action. This normative message will read *“In similar studies, the majority of people decided to donate some of the money should they win it,”* followed by a question about the participants’ willingness to donate (see Table 1). Although the normative imessage could be stronger than the one suggested (i.e., “*In*

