#### Descriptive Norms

Similarly to several previous studies (e.g., Smith and McSweeney, 2007; Croson et al., 2009; van der Linden, 2011), descriptive norms will be assessed with the following items: “How likely do you think is that people you know would donate to this charity?” (1 – very unlikely; 7 – very likely); “How much do you think an average person doing this survey would donate if they won the gift card?” (1 – nothing; 7 – all of it); “How many of the people you know would donate to this charity?” (1 – none of them; 7 – all of them); “How many of the people doing this survey would donate to this charity?” (1 – none of them; 7 – all of them). In previous studies, the reliability of similar four-item measurements of descriptive norms was found to be *p* = 0.76 (Smith and McSweeney, 2007).

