## Stepwise Procedure

This experimental study uses a 3 (morally (in)congruent/neutral calls-to-action) × 2 (presence/absence of social norm) between-subjects design and can be conducted online through a custom developed app or existing survey platform. The study procedure can be split into eight steps. (1) Firstly, participants receive a brief description of the study and its goals (e.g., “we want to explore the relationship between morality and CB and test the effectiveness of appeals to donate”) and are asked to provide informed consent for participation. (2) Secondly, participants complete the MFQ and the Moral Internalization subscale. (3) Thirdly, participants are asked to complete a basic demographic questionnaire. (4) Thereafter, the participants are randomly assigned to one of the two different charity causes and to one of six different experimental conditions. We use random assignment to ensure that samples are similar across conditions in terms of observed and unobserved characteristics. After the experimental exposure, participants are first asked about their attitudes toward charitable behavior and perception of social norms regarding the CB (5) and are then asked to indicate their willingness to donate (a) time and (b) money to the charity they were presented (6). The sequence of presenting the questions to donate time versus money will vary randomly in order to minimize the potential influence of sequence on both donation measures. Next, the participants are provided with a feedback regarding their scores on the MFQ and moral identity internalization questionnaire (7). Finally, an optional step is asking permission to collect participants’ Facebook data. Participants can either accept or deny this request. Regardless of their choice, in the last step, debriefing about the study and contact for further inquiries are provided (8). See Figure 2 for a visualization of this procedure.

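### Only the binding call refers to other people's conduct, so its effect may mix moral fit with social information, and the mediation plan has no path that would show it

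*Protocol article*

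**What the plan says.** The Stepwise Procedure section describes a 3 × "2 (presence/absence of social norm) between-subjects design". The Normative Information section makes the second factor a single sentence: "Normative information will either be included or omitted in addition to the calls-to-action". The sentence reads "In similar studies, the majority of people decided to donate some of the money should they win it".

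Table 1 gives the three texts. The binding text offers the reader the chance to "follow proud religious and national leaders doing their obligation". The individualizing and neutral texts say nothing about anyone else's conduct. The clause about leaders is bold, and the table note explains that "Bolded words represent the individualizing and binding moral frames", so it is an intended part of the moral frame. It appears in the binding call with and without the norm sentence.

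The introduction defines a descriptive norm as "conveying information about what most others actually do". The pre-study asked participants to rate "the degree to which each of the calls-to-action rely on each of the five foundations"; no rating of perceived norms is reported. In the main study, attitudes and perceived norms are measured in every cell, after exposure and before the donation questions.

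The Statistical Analysis section plans a MANOVA with call congruence, norm and their interaction. Its mediation analysis has two separate routes: call to attitudes to charitable behavior, and norm sentence to perceived norms to charitable behavior.

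**The concern.** The protocol wants to learn two things from the calls: whether a morally fitting appeal raises giving, and whether it does so by shifting attitudes. Both readings need the call texts to differ in moral frame and not also in what they tell the reader about other people. The binding text may not meet that condition. Saying that leaders are meeting an obligation, and inviting the reader to follow them, can suggest that others already act.

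Two readings are at stake. For participants with a binding profile, the congruent-versus-neutral comparison could contain a response to social information as well as moral fit. The Anticipated Results section makes a specific prediction from this text: a larger impact of the binding call for the refugee charity among people high on binding foundations. Second, if the binding text moves perceived norms, the planned mediation model has no path for it. The effect would then appear as a direct effect of the call, or be credited to attitudes so far as attitudes and perceived norms are correlated.

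**Working it through.** **1. The plan's own figure.** A Pillai-type MANOVA calculation was used, with f² = 0.02, α = 0.05, two outcomes and three effect degrees of freedom (λ = N·s·f², s = 2, df1 = 6). It gives power 0.9003 at N = 439 and 0.8003 at N = 344. Both stated sample sizes reproduce, and this point does not dispute them.

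**2. Where the clause acts.** Write m for the neutral call without the norm sentence, b for the moral framing of the binding text, s for any effect of the leader clause as social information, n for the effect of the norm sentence, and k for any overlap between the two cues. None of b, s, n or k is given in the documents.

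| Cell | Without sentence | With sentence | Difference |
|---|---|---|---|
| Neutral | m | m + n | n |
| Binding | m + b + s | m + b + s + n − k | n − k |

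- Norm contrast within the binding call: n − k. The term s has gone.
- Binding minus neutral without the sentence: b + s.
- Binding minus neutral averaged over both norm levels: b + s − k/2.

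So s stays in the call comparison whatever k is. It never enters the norm contrast; only k does.

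**3. The same under congruence coding.** The planned factor is congruent, incongruent or neutral. Let π be the share of analysed participants with a binding profile, and assume that s is the same in both profiles and k = 0. The binding text is the congruent call for the share π and the incongruent call for the share 1 − π. The pooled contrasts then carry:

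- congruent minus neutral: π·s
- incongruent minus neutral: (1 − π)·s
- congruent minus incongruent: (2π − 1)·s

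With an assumed even split (π = 0.5), s drops out of congruent versus incongruent but adds s/2 to each comparison with neutral. Within the binding profile, congruent minus incongruent carries the whole of s; within the individualizing profile it carries −s.

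**4. What overlap would do.** Let k = c·n, with c assumed between 0 and 1. The average norm effect over the three texts is n(1 − c/3), and the binding-versus-other-texts interaction contrast is c·n. In standard-deviation units, with n = d:

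| d | c = 0 | c = 0.5 | c = 1 |
|---|---|---|---|
| 0.20 (the protocol's illustration of a small effect) | 0.200 | 0.167 | 0.133 |
| 0.58 (the norm effect the protocol cites) | 0.580 | 0.483 | 0.387 |

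At c = 0 there is neither dilution nor interaction. If the cues reinforce each other (k negative), the norm effect grows and the interaction changes sign. Under congruence coding with an even split, the interaction contrast is moral versus neutral and halves to c·d/2. At d = 0.2 and c = 1 that is 0.10, detected about 8% of the time at N = 439, against 5% by chance.

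**5. The mediation paths.** There are four possible first-stage paths: call to attitudes, call to perceived norms, norm sentence to attitudes, norm sentence to perceived norms. The plan names the first and the last. The second is the one the binding text could open, and both mediators are already collected in every cell.

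**The case against.** The strongest reply is that the clause is the manipulation itself. The binding frame is meant to draw on Authority, and Authority showed the widest pre-study gap between the two moral calls (4.90 against 2.72, a difference of 2.18 scale points). Leaders are also not most others, so the clause fits the protocol's definition of a descriptive norm only loosely. It does not say that anyone gave to this charity. The perceived-norm items ask about acquaintances and survey participants, as in "How many of the people doing this survey would donate to this charity", not about leaders. Language of duty does not settle it either, since the individualizing text also tells the reader what is morally right. All of this stands, and it is why the point is a possible confound and not an error in the norm factor. It does not show that the binding text leaves perceived norms unchanged; nothing reported tests that.

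A reader might infer something stronger: that the wording alone biases the norm effect toward zero, builds in a call × norm interaction and costs power. The documents do not support this. The clause is in both binding cells and cancels unless the cues are sub-additive. One can make the loss look large: with d = 0.28 and an outcome correlation of 0.3, two-outcome power at N = 439 is 91%, 78% and 57% at c = 0, 0.5 and 1. But c and the correlation are assumptions, and 0.28 is the low end of a range that the protocol cites for moral framing, not for norms. At its cited norm effect of 0.58, the same calculation stays above 99% for every c.

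Finally, a condensed article may leave estimates by text to an analysis plan. That is fair for the sensitivity analysis. The mediator assigned to each factor, however, is stated in the article.

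**Conclusion.** The point holds as a limit on interpretation. Only the binding call refers to others' conduct. Any effect of that reference is mixed into comparisons involving the binding text, and the mediation plan cannot separate it. This needs no assumption about how the two cues combine, only that the clause has some effect as social information. The size of that effect cannot be derived from the documents. By algebra, with an even split of profiles and the same response in both, half of it enters the pooled congruent-versus-neutral comparison, none enters congruent versus incongruent, and all of it enters the contrasts within the binding profile.

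A weaker norm effect or a call × norm interaction is only a possibility, conditional on overlap that the documents neither state nor quantify. No power loss and no change to the sample size follow. Figure 1 and the appendices were not available for this check, so it rests on the text of the Aims, Table 1, Pre-study and Statistical Analysis sections.

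**What to change.** In the analysis:

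- Enter attitudes and perceived descriptive norms as parallel mediators for both factors, including the path from call text to perceived norms.
- As a planned sensitivity analysis, report mean perceived norms and the norm effect separately for the individualizing, binding and neutral texts.

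This uses data the protocol already collects. The cost is a few extra estimates with less precision. At N = 439 in six equal cells (about 73 each), the norm effect within one text has a standard error of √(2/73.2) = 0.165 SD, against √(4/439) = 0.095 SD for the pooled effect, a factor of √3. The estimates by text should therefore be read as descriptive.

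Optionally, before fielding, have a small sample rate the three calls without the norm sentence on the perceived-norm items. Reword the clause only if the binding call shifts those ratings and its Authority rating can be kept; otherwise rewording could weaken the intended contrast. This costs a short rating exercise and, if needed, one clause re-translated in each language.
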